#### 5.5 Definitions

##### 5.5.1. Days

Day 1 is from time of randomization to start of new 24 hr period as per local protocol. Day 2 is next 24 hr period. The last day of ICU stay is from the start of new 24 hr period as per local protocol until discharge.

##### 5.5.2. Fluid balance

Fluid balance is calculated as sum of all input of enteral and parenteral fluids minus all measured losses. Estimated loss through evaporation will not be included in fluid balance. Stool will not be included in balance unless the patient has a faecal management system or similar device in place.

##### 5.5.3. Protocol deviations

Protocol deviations include randomization of a non-eligible patient and non-compliance with treatment algorithm in the intervention and control arms as described above.

#### 5.6 Co-enrolment

We will encourage co-enrolment with other interventional trials, unless the trial protocols are incompatible. Co-enrolment agreements will be established with the sponsor/principal investigator of such trials and a list of trials approved for co-enrolment will be available to the investigators.

### 6. Data collection

Clinical, laboratory and background data will be collected at the time of enrolment, during the ICU-stay, at ICU-discharge and at follow-up. Data will be obtained from hospital records,

and relatives and close friends of the patient, and will be entered into a web-based electronic case report form (eCRF) by site personnel. Data from the web-based forms will be migrated to a trial database, which will be handled by the coordinating team. The sponsor supplies a standard description of all units of measurement in the eCRF. If a trial site uses different units of measurement and this might be a potential source of error, the site investigator should contact the coordinating team to have the data capture module modified. Data not obtainable will be registered as missing and measures to obtain data should not delay intervention or concomitant treatment. All efforts will be made to collect data on the primary and secondary outcomes for patients transferred to a non-REDUSE ICU. Fluid data will be collected as long as the patient receives the intervention. A detailed description of data is provided in Appendix A

### 6.1 Quality control of data

Site principal investigators will be responsible for training clinical staff on correctly entering variables into the electronic case report forms (eCRFs). Particular emphasis will be placed on recording fluid administration and fluid balance data in a standardized manner. Instructions will be available in the trial master file and eCRFs. All sites will receive a site initiation visit via a digital meeting from an independent monitor before the start of inclusion. Moreover, monitors will visit all sites when 10 participants have been included. The visits will include control of routines for data collection and entry as well as quality control of data by source data verification. To minimize missing data and ensure adherence to the protocol we will use central monitoring and we will develop a central monitoring plan before the start of the trial. The site investigator must sign all eCRFs before trial completion to verify that the recorded data is correct and complete.

### 6.2 Biobank

We will collect blood samples at baseline, 3 days , and 5 days after randomization. At each time point we will collect 12 ml of blood. Blood samples will be processed and aliquoted according to a separate protocol. All samples will be transported to and stored in a central biobank after the trial is completed . Samples may be analysed for routine clinical laboratory measurements and prognostic biomarkers, including markers of neuronal injury, inflammation, and mitochondrial content. No analysis will occur before the trial ends, and no results from the biobank will be published in the initial manuscript. Participation in the biobank will be optional for each site.

## 7. Ethics and Informed consent

Ethics applications will be submitted to the National Research Ethics boards of participating countries. The applications will seek approval for a deferred consent process. This is based on the premise that to have the greatest possible impact; the intervention has to be started as soon as possible after admission to the ICU. Because cognitive symptoms are hallmark symptoms of septic shock, we regard it as impossible in most cases to obtain an informed consent at the time of presentation (Singer, 2016). We judge that this strategy is justifiable according to the Declaration of Helsinki article 30 available from the World Medical Association. Surviving participants will be asked for written consent as soon as they are able to make an informed decision. The participants will be provided with written and oral information on this trial to make an informed decision about participation in the trial. A

participant who does not give consent will be asked if already collected data can be used. The consent form must be signed by the participant. At Swedish sites, a member of the research team will approach the legal representative or a personal consultee (relative or close friend) as soon as practically possible to inform about the trial and seek their opinion about the participation of the patient in the trial.

## **8. Data management**

### **8.1 Data handling and record keeping**

Individual patient data will be handled as ordinary chart records and will be kept according to the legislation (e.g., data protection agencies) of each participating country. Data will be entered into a web-based electronic case report form (eCRF). The electronic data capture module fulfils criteria for handling of patient data according to the Swedish legislation on management of personal data and will be compliant with the General Data Protection Regulation of the EU (European Parliament and Council of the European Union directive 2001/20/EC) and with the Federal Drug Administration's guidelines for electronic signatures (FDA 21 CFR Part 11 Guidelines for Electronic Signatures). All original records will be retained at trial sites or at the principal investigator for 15 years to allow inspection by relevant authorities. The trial database will be maintained for 15 years.

### **8.2 Quality control and quality assurance**

The trial will be externally monitored by national monitoring offices coordinated by the clinical trial manager and Clinical Studies Sweden, Forum South. All variables will be collected in a participant-specific trial ledger or directly in the eCRF. Site principal investigators will be responsible for training clinical staff on how to enter variables correctly. Special emphasis will be given to how to record fluid administration and fluid balance in a standardized manner. Instructions will be available in the trial ledger and in the electronic case report forms (eCRFs). All sites will have a site initiation meeting with monitors before start of inclusion and a closeout visit at end of study. Moreover, all sites will be visited by monitors when about 10 participants from that site have been included. The visits will include control of routines for data collection and data entry as well as quality control of data by comparing selected source data with data entered in eCRFs. The site investigators will be responsible for entering all relevant data into the electronic CRFs. The CRFs will be constructed in order to ensure data quality with predefined values and ranges on all data entries. To further optimize completeness and quality of data we will also use central data monitoring. A detailed central data monitoring plan will be developed before inclusion of 100 patients in the trial.

## **9 Adverse events**

Detection, documentation and reporting of adverse events will be the responsibility of the local investigator.

### **9.1 Definitions**

Patients with septic shock in the ICU experience a host of adverse events. Only a small number of those could be considered to be related to the intervention. In addition to the patient-centred complications described above we will monitor patients for;

- Suspected unexpected serious adverse events (SUSAE) (an adverse event not reasonably explained by other factors than the intervention which may cause death or be life threatening, prolong hospitalisation or may result in significant disability/incapacity)

## 9.2 Reporting of SUSAEs

All SUSAEs observed by the investigator or other caregivers must be recorded in the eCRF. The circumstances of a SUSAE should be described and should be reported to the principal investigator within 48 hrs. The causality between the trial intervention and the SUSAE should be assessed by the site investigator. The local investigator is required to follow the participant until resolution of symptoms. Reports of a SUSAE will be assessed for safety by a qualified physician in the trial management team (medical monitor). SUSAEs will be reported to the DSMC within 3 days of reaching the steering group.

## 10. Statistical analysis plan

A detailed statistical analysis plan will be published before the randomization of the last participant. In short, data will be analysed by two independent statisticians blinded to the treatment on an intention-to-treat basis. The intention-to-treat population is defined as all randomized patients who consented to use of their data. The per-protocol population is defined as all randomized patients fulfilling all inclusion criteria and no exclusion criteria who consented to use of their data, and excluding those having one or more protocol deviations as defined above (5.5.3). Patients will be considered to be included in the trial when they are randomized.

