#### 4.4 Exit from the trial

A participant or his/her surrogate is free to withdraw from the trial at any time. A participant will exit the trial if the participant withdraws her/his consent. The participant making the withdrawal of consent will be asked for permission to use the data acquired up to that time point and if data for the primary endpoint can be collected. If permission is obtained, the participant will be included in the final analyses. If the participant declines, all data with the exception of initials, sex and date of withdrawal will be destroyed. If the trial intervention is discontinued by the treating physician because of adverse events, if the participant is withdrawn from active care and/or the focus of care is changed to palliation, or any other reason, this does not constitute withdrawal from the trial and the participant will not exit the trial (data collection will continue). A participant transferred to a non-REDUSE ICU will not exit the trial. All participants randomized in this trial will be analysed on an intention-to-treat basis.

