#### 5.1 Screening and randomisation

Clinical investigators at each participating ICU will be responsible for screening of all admitted patients with a diagnosis of septic shock. A screening log will be compiled while the trial is active at each site and will include all adult patients with an admission diagnosis of septic shock whether they are eligible for inclusion or not. We will document reasons for not including an eligible patient. Informed consent will be obtained as specified in each national ethical approval. Trial sites will have access to an internet-based randomization application within the eCRF to allow for immediate allocation and adequate generation and concealment of the allocation sequence. Each patient will be assigned a unique trial number. Randomization will be performed with permuted blocks of varying block size unknown to the trial investigators, stratified for trial site.

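### The intention-to-treat set requires positive consent, but consent is deferred and sought from survivors, so the definition as written leaves out patients who die before being asked

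*Protocol*

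**What the plan says.** Section 10 of the protocol defines the primary analysis set: "The intention-to-treat population is defined as all randomized patients who consented to use of their data". The per-protocol set repeats the consent condition and adds eligibility and the absence of protocol deviations.

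Section 7 describes how consent is obtained. "The applications will seek approval for a deferred consent process". After that, "Surviving participants will be asked for written consent as soon as they are able to make an informed decision", and "The consent form must be signed by the participant". At Swedish sites a legal representative or personal consultee is approached to "inform about the trial and seek their opinion about the participation of the patient in the trial"; this is not described as consent to the use of data. Section 5.1 adds that "Informed consent will be obtained as specified in each national ethical approval", without giving the national details.

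Section 4.4 covers exit from the trial. It removes data only after a refusal: "If the participant declines, all data with the exception of initials, sex and date of withdrawal will be destroyed". It closes with: "All participants randomized in this trial will be analysed on an intention-to-treat basis".

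The primary outcome (section 3.1) is all-cause mortality at 90 days. Section 10.1.1 assumes 45% mortality under usual care and raises the required 1808 patients to 1850 for loss to follow-up and lack of consent together.

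**The concern.** Section 10 sets an opt-in test, whereas section 4.4 sets an opt-out test. The two agree for every patient who is asked and answers. They part for patients who are never able to answer: those who die before regaining capacity and those who never regain it. Under section 10 these patients have not consented and are outside the set. Under section 4.4 they have not declined and are inside it.

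In most trials such a group would be a small nuisance. Here the patients have septic shock, consent follows randomisation, and the outcome is death. Under the literal rule, membership of the analysis set depends partly on the outcome being analysed. That would lower the event rate, change the risk difference and the risk ratio, and cost power. If the timing of deaths relative to consent differed between arms, it would also undo the protection that randomisation gives. A later analysis plan that copies section 10 inherits the problem, and one that departs from it contradicts the protocol.

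**Working it through.** **Inputs from the protocol.** 1:1 allocation (section 5); 90-day mortality 45% against 37.5%, that is, a 7.5-point absolute reduction, alpha 5%, power 90%, required N 1808, planned N 1850 (section 10.1.1). Sidedness is not stated; two-sided is assumed.

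**The protocol's own figure.** With pooled variance and no continuity correction,

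n per arm = [z(0.975)·√(2·p̄·(1−p̄)) + z(0.90)·√(p1(1−p1) + p2(1−p2))]² / (p1−p2)²,

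where p̄ = 0.4125. This gives [1.960·0.6962 + 1.282·0.6942]² / 0.075² = 903.3, so 904 per arm and 1808 in total, as stated. The allowance is 1850 − 1808 = 42, and 42/1850 = 2.3%.

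**Expected deaths at 925 per arm.** 925 × 0.45 = 416 and 925 × 0.375 = 347, together 763, or 41% of 1850.

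**Effect of the literal rule.** Let f be the share of deaths that precede consent. The protocol does not give f, so a range is assumed, equal in both arms, with all survivors consenting. In an arm with true mortality p:

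- patients analysed = 925·(1 − f·p)
- analysed mortality = p(1 − f)/(1 − f·p)
- power = Φ{[|p1−p2| − 1.960·√(p̄(1−p̄)(1/n1 + 1/n2))] / √(p1(1−p1)/n1 + p2(1−p2)/n2)}, with p̄ pooled over the patients who remain

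| f | Deaths excluded | N analysed | Control vs intervention | Difference (points) | Risk ratio | Power |
|---|---|---|---|---|---|---|
| 0 | 0 | 1850 | 45.0% vs 37.5% | 7.5 | 0.83 | 91% |
| 5% | 38 | 1812 | 43.7% vs 36.3% | 7.4 | 0.83 | 90% |
| 25% | 191 | 1659 | 38.0% vs 31.0% | 7.0 | 0.82 | 85% |
| 50% | 382 | 1468 | 29.0% vs 23.1% | 6.0 | 0.79 | 74% |
| 75% | 572 | 1278 | 17.0% vs 13.0% | 3.9 | 0.77 | 51% |
| 90% | 687 | 1163 | 7.6% vs 5.7% | 1.9 | 0.75 | 26% |

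The 42-patient allowance is used up at f = 42/763 = 5.5%, before any refusal or loss to follow-up.

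**The odds ratio.** Removing the same share of deaths from both arms multiplies the odds of death in each arm by (1 − f). The ratio stays at (0.375/0.625)/(0.45/0.55) = 0.733 for every f below 1. With equal shares, then, the effect is a smaller risk difference, a shifted risk ratio and lost power. It is not a false effect.

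**Unequal shares under the null.** Take 45% true mortality in both arms, and exclude 50% of control deaths but 40% of intervention deaths (both shares assumed):

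- control: 0.45·0.5/(1 − 0.45·0.5) = 0.225/0.775 = 29.0%
- intervention: 0.45·0.6/(1 − 0.45·0.4) = 0.270/0.820 = 32.9%

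With 717 and 758.5 patients expected to remain, the two-sided 5% test rejects about 37% of the time although there is no effect.

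**The case against.** A reader might infer that the trial will drop its deaths, losing most primary events and ending with power near 26%. The documents do not support that.

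- Section 4.4 takes data out only after a refusal, and says that a change to palliative care is not withdrawal.
- The 45% mortality assumption and the 2.3% allowance make sense only if deaths before consent are counted.
- Section 10 itself regards patients as included once randomised.
- The consent fields in Appendix A record separately whether the patient was informed, why not, whether consent was given, and whether data may be used. Patients never asked can therefore be told apart from those who refused.
- National approvals may cover deceased patients. The model consent form (Appendix E) was not available to read, so its silence cannot be counted against the plan.

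A reader might also infer that the rule would be improvised once results are known. Section 10 promises a detailed analysis plan before the last randomisation, and sections 5.4 and 10 keep the statisticians blinded, so that does not follow either.

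It can fairly be added that section 4.4 is not literally about all randomised patients, because refusers' data are destroyed. Section 10 may be loose shorthand for that exception.

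All of this speaks to intent, and it stands. It does not repair the definition. Consenting and not refusing are different conditions, and they differ for exactly the patients who supply outcome events. The protocol does not say how a patient who was never asked is classified.

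**Conclusion.** The definition is wrong as written; this is not merely detail left for later. Sections 7 and 10 taken together make survival to consent a condition of entering the primary analysis set, and section 10 conflicts with the refusal-based rule in section 4.4. The probable intent is to keep everyone who does not refuse.

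The size is conditional twice over: on the rule being applied literally, and on the unstated share of deaths before consent. Across assumed shares of 5% to 90%, equal in both arms and with all survivors consenting, power runs from about 90% to about 26%; the low end is a worst case, not an expectation. Over the same range the risk ratio moves from 0.83 to 0.75 while the odds ratio stays at 0.733. Bias under the null needs a share that differs between arms; the 37% false-rejection figure rests on an assumed 50% against 40%.

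**What to change.** In section 10, define the intention-to-treat set as all randomised patients except those for whom use of data was actively refused by the participant, or by a representative where the national approval gives that right. State that patients who die or remain incapacitated before being asked are retained where the national approval permits. Use the same consent wording for the per-protocol set, bring the closing sentence of section 4.4 into line with it, and carry it into the statistical analysis plan. Report exclusions by arm.

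The cost is a few sentences. No additional data are needed and the sample size stands: 1808 analysed patients give 90.0% power and 1850 give 90.7%.

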### 10.1 Sample size

#### 10.1.1 Primary outcome

The sample size calculation is based on an expected 90-day mortality of 45 % in the control group (Hjortrup 2016, Perner 2012, Hernandez 2019, Holst 2014). To detect an absolute reduction in mortality of 7.5%, with an  $\alpha$  of 5% and a power of 90% the required sample size is 1808. We chose 7.5% as anticipated intervention effect because it is a realistic and clinically relevant effect size observed in previous large intensive care trials assessing interventions in critically ill patients (Perner 2012, Andersen-Ranberg 2023). To account for loss to follow-up and no-consent from some patients we will include a total of 1850 patients.

#### 10.1.2 Secondary outcomes

Based on a minimally important relative risk reduction of 20% and a rate of complications in the control group of 30%, the sample size yields a power of 99% for the complications outcome (Meyhoff 2022).

Based on a minimally important difference of 2 days, and the data collected in the REDUSE feasibility trial (Lindén 2024), we used simulations to ascertain the power using Van Elteren as the primary analysis. Using 1,000 iterations, we found a power of 80% mechanical ventilation-free days outcome.

Based on a minimal important difference of 1.5, a standard deviation of 2.8, (Hodgson 2022) the sample size yields a power of 100% for the MOCA-BLIND score outcome.

Based on a minimal important difference of 5 points, a standard deviation of 20 points, the sample size yields a power of 99% for the EQ-VAS score outcome (Contrin 2013, Granja 2004, Hammond 2020).

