### 3.4 Rationale for primary and secondary outcomes

Several observational studies have reported an association between a positive cumulative fluid balance and mortality (Boyd 2011, Marik 2017, Sakr 2017, Silversides 2018).

Because less administration of non-resuscitation fluids could decrease intravascular volume and therefore increase ischemia and acute kidney injury, we will assess the incidence of ischemic complications and acute kidney injury. Previous trials assessing effects of restrictive

administration of resuscitation fluids in sepsis have found no effect or a decreased incidence of acute kidney injury (Douglas 2020, Hjortrup 2016, Meyhoff 2022)

Days alive and free of mechanical ventilation is a patient-important outcome and is also essential to assess potential effects on healthcare costs. Strategies to reduce fluid overload in patients suffering from acute respiratory distress syndrome have been suggested to increase the number of days alive and free of mechanical ventilation (Wiederman 2006).

Cognitive impairment and decreased HRQoL are common after sepsis (Hammond 2020, Iwashyna 2013, Kjær 2023). Restrictive fluid administration has been associated with impaired cognitive function in patients suffering from acute respiratory distress syndrome (ARDS) (Mikkelsen 2012). No differences in HRQoL and cognitive function could be demonstrated by restricting resuscitation fluids in septic shock in the recent CLASSIC trial but clinically important differences could not be excluded (Kjær 2023). Based on a modified Delphi process involving patients and researchers (<http://www.improvelto.com>), the performance-based cognitive screening measure MoCA and the patient-reported outcome measure EQ-5D-5L have been the recommended tests for cognitive function and HRQoL in patients with acute respiratory failure, a common organ failure in septic shock (Needham et al 2017). These tests have been used in large trials in septic shock and have been translated into many languages including Swedish (Kjær 2023, Hammond 2020).

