## 10.2 Analysis methods

Analyses will be performed according to an intention-to-treat principle. All analyses will be adjusted for site of admission. All analyses will be adjusted for site of admission. The primary outcome and the first secondary outcome (complications) will be analysed using mixed effects logistic regression with site as a random intercept. RR will be estimated using the 'nlcom' STATA command or G-computation in R (R Core Team, Vienna, Austria). Count data (mechanical ventilation-free days) will be analysed by van Elteren test with site as a covariate. Secondary continuous outcomes (MoCA-BLIND and EQ-VAS) will be analysed using mixed effects linear regression with site as a random intercept.

All primary conclusions will be based on our primary outcome and, a priori, secondary and explorative outcome results will be considered as hypothesis generating. Based on this we will consider a P-value of 0.05 as a threshold for statistical significance for all analyses.

All primary conclusions will be based on our primary outcome and, a priori, secondary and explorative outcome results will be considered as hypothesis generating. Based on this we will consider a P-value of 0.05 as a threshold for statistical significance for all analyses.

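### The 99% power stated for the complications outcome is wrong: the protocol's own inputs give about 82% to 83%

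*Protocol*

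**What the plan says.** Section 10.1.2 bases the power for the complications composite on a "minimally important relative risk reduction of 20% and a rate of complications in the control group of 30" per cent, and concludes that "the sample size yields a power of 99% for the complications outcome".

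The sample size meant is the one in section 10.1.1, set by 90-day mortality: with an alpha "of 5% and a power of 90% the required sample size is 1808", raised for loss to follow-up and missing consent so that "we will include a total of 1850 patients". Section 5 fixes 1:1 allocation. Section 10.2 says that "we will consider a P-value of 0.05 as a threshold for statistical significance for all analyses". No other input to the 99% is given.

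Section 3.4 gives the reason for measuring complications: "Because less administration of non-resuscitation fluids could decrease intravascular volume and therefore increase ischemia and acute kidney injury".

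**The concern.** A 20% relative reduction from 30% is an absolute difference of 6 percentage points. The primary outcome, with a difference of 7.5 points from a 45% control rate, has 90% power at the same sample size. The smaller variance at 30% against 24% does not make up for the smaller difference, so a figure of 99% for complications is implausible on sight.

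What is at stake is how the result is read. Complications is the first secondary outcome, and it addresses a specific safety question, namely whether giving less fluid causes ischaemia or severe kidney injury. If power is believed to be 99%, a non-significant result looks like near-conclusive evidence against an effect of the size that the protocol calls minimally important. If power is nearer 82%, an effect of that size would be missed about once in every five or six trials.

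**Working it through.** **Inputs**

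| Input | Value | Source |
|---|---|---|
| Control complication rate, p1 | 0.30 | Protocol 10.1.2 |
| Relative reduction | 20%, so p2 = 0.30 × 0.80 = 0.24 | Protocol 10.1.2 |
| Total patients | 1808 required, 1850 planned | Protocol 10.1.1 |
| Allocation | 1:1, so n = 904 or 925 per arm | Protocol 5 |
| Alpha | 0.05 | Protocol 10.1.1 and 10.2 |
| Sidedness | Not stated; two-sided assumed | Supported by step 1 |

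**Step 1. Reproduce the protocol's primary figure.** The pooled-variance formula for two proportions, with p̄ = (p1 + p2)/2, is

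n per arm = [1.960 × √(2p̄(1−p̄)) + z(power) × √(p1(1−p1) + p2(1−p2))]² / (p1 − p2)²

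For mortality, 0.45 against 0.375 at 90% power (z = 1.2816):

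- first term: 1.960 × √(2 × 0.4125 × 0.5875) = 1.3645
- second term: 1.2816 × √(0.2475 + 0.2344) = 0.8896
- n = (1.3645 + 0.8896)² / 0.075² = 903.3, so 904 per arm and 1808 in total

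This is exactly the protocol's number, which supports both the formula and the two-sided test.

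**Step 2. Apply the same formula to complications.** Here p̄ = 0.27 and

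power = Φ{ [0.06 − 1.960 × √(2 × 0.27 × 0.73 / n)] / √[(0.30 × 0.70 + 0.24 × 0.76) / n] }

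- n = 904: (0.06 − 0.04093) / 0.02083 = 0.915, so power = 82.0%
- n = 925: (0.06 − 0.04046) / 0.02060 = 0.949, so power = 82.9%

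A simulation of the pooled z test (400,000 replicates) gives the same 82.0% and 82.9%.

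**Step 3. Look for a reading that gives 99%.**

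| Variant (30% against 24% throughout) | N=1808 | N=1850 |
|---|---|---|
| Unpooled variance | 82.1% | 83.0% |
| Arcsine | 82.1% | 82.9% |
| Log relative risk | 81.6% | 82.5% |
| Log odds ratio | 81.8% | 82.7% |
| Continuity-corrected | 80.6% | 81.5% |
| One-sided 5% | 89.1% | 89.7% |
| Total N entered as N per arm | 98.2% | 98.4% |

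Only the last row comes near the stated figure, and it doubles the trial. It may be how the slip arose, but that is inference.

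**Step 4. What 99% would require.** With z = 2.326, n = (1.2306 + 1.4573)² / 0.06² = 2,006.8, so 2,007 per arm and 4,014 in total. With 1850 patients, 99% needs either a relative reduction of about 29% (30% against about 21%) or a control rate of about 49% with a 20% reduction. The protocol states neither.

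**Step 5. Sensitivity.** Section 10.3 expects less than 5% missing data for this outcome. At that limit, with about 1757 of 1850 patients analysed, power is 80.9%. For a relative increase of the same size (30% to 36%), power is 77.5% with 1808 patients and 78.4% with 1850.

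**The case against.** The arithmetic is not seriously contestable; the arguments on the other side concern its weight.

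- **Consequence for the trial.** Section 10.2 rests all primary conclusions on mortality and calls secondary results hypothesis generating. The sample size comes from mortality alone and is correct. Changing the complications power changes no threshold, analysis or stopping rule. This stands, and it limits the damage to interpretation.
- **Adequacy.** The corrected power is still above 80%, the level reported in the same section for ventilation-free days. This stands too: the outcome is not shown to be badly powered; its power is misreported.
- **Reading of a null result.** Nothing in the protocol says that a non-significant result will be taken to exclude an effect, and section 10.2 plans a relative risk estimate. That is fair. The confidence interval should govern the reading, but a published 99% invites the wrong one.
- **Other harm measures.** Mortality, cognition, metabolic and catheter events and serious adverse events also bear on safety, and the protocol does not rank complications above them. That is correct, although section 3.4 still makes this the outcome for ischaemia and kidney injury.
- **Model.** The planned analysis is a mixed-effects logistic regression with a random site intercept, not a simple two-proportion test. No site variance is given, but such adjustment would not be expected to lift power from about 83% to 99%.
- **Harm direction.** The protocol powers this outcome for a reduction only, so the 77.5% to 78.4% for an increase corrects no stated number. It is useful additional information, not part of the error.

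**Conclusion.** The stated 99% is wrong. On the protocol's own inputs the power is 82.0% with 1808 patients and 82.9% with 1850, an overstatement of 16 to 17 percentage points. The type II error for the effect that the protocol calls minimally important is about 17% to 18%, not 1%.

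This rests on a two-sided 5% test, which the primary calculation supports, on 1:1 allocation, and on complete data. Missing data at the 5% limit would lower power to about 81%. No standard choice of test with the correct total reaches 99%, and even a one-sided 5% test stays below 90%. The error affects a reported figure and how the first secondary outcome would be read. It does not affect the primary sample size or the primary conclusion.

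**What to change.** In section 10.1.2, replace 99% with about 82% (1808 patients) or about 83% (1850 patients), and write out the comparison as 30% against 24% with a two-sided 5% test. If 99% was obtained from other inputs, state them. The 20% reduction should not be enlarged merely to keep the number, because the protocol presents it as the minimally important effect.

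As an optional addition, since section 3.4 is concerned with harm, state that power for a 20% relative increase (30% to 36%) is about 77% to 78%.

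Section 10 says that a detailed statistical analysis plan will be published before the last participant is randomised; the 99% should not be carried into it. The cost is one corrected sentence and a less favourable figure, with no additional patients and no change to the design or analysis.
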